#### Primary aim

The primary aim analysis will determine the effect of the most intensive adaptive implementation intervention, by comparing the total number of CBT sessions delivered by SPs over the course of 18 months between schools receiving REP alone (the control) versus schools receiving the adaptive intervention (REP + coaching + facilitation for schools that are eligible).

#### Exploratory aims

For exploratory aim 1 analyses, incremental cost effectiveness ratios (ICERs) will be calculated for each relevant comparison of implementation interventions by dividing the incremental average costs by the number of CBT sessions delivered as well as the number of depression or anxiety-free days based on PHQ-9T or GAD-7 student score changes between each time point.

Exploratory aim 2 analyses will assess whether the implementation intervention effectiveness is moderated by SP or school-level factors including SP prior training and baseline perceptions of CBT, as well as perceived school administrator support for adoption of CBT. Results of these analyses will be used to construct a more deeply tailored adaptive implementation intervention that further improves uptake, and particularly SP delivery of CBT.

Exploratory aim 3 analyses will test mechanisms through which the coaching and facilitation implementation strategies increase frequency of CBT delivery and/or improve student mental health outcomes.

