#### Exploratory aims:

To estimate the costs of different implementation interventions and determine the incremental cost-effectiveness of added coaching and/or facilitation.To assess whether the effect of augmenting REP with coaching or facilitation is moderated by SP or school factors such as SP knowledge and perceptions of CBT as well as school administrator support of CBT implementation.To determine whether coaching and facilitation improve CBT knowledge, perceptions, skills, or championing skills among SPs, and which of these account for increases in frequency of CBT delivery and improvement in student clinical symptoms.

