#### Cost estimates

For each implementation strategy, we will calculate the average costs and average outcomes per SP using methods described elsewhere [39]. The primary implementation costs are the personnel time spent in REP activities (e.g., SP training, TA), coaching (e.g., time to hire/train coaches, network maintenance, SP coaching time), and facilitation by study participants (including SP and school administrator time). Costs will be quantified as hours multiplied by wages and fringe benefits for each person. Wage rates will be obtained from school records, and in cases where this information is not available, average wages for each occupational level will be used from the Bureau of Labor Statistics. Hours will be tracked through attendance logs for each implementation activity.

To assess costs of delivering CBT, 40 randomly selected SPs will also be asked to complete time-motion surveys for 2 weeks (starting 4 weeks after the phase 2 randomization) that ask about time allotted to providing CBT versus other forms of student counseling, care, or crisis management. School services will be translated to costs based on the wage rates of school providers.

Student-level service costs of CBT delivery and other use will also be estimated from study records of participation in CBT sessions, academic indicators, and self-reported utilization survey data on inpatient, emergency department, and outpatient use outside the school setting. Health care costs will be assigned using Current Procedural Terminology (CPT) codes, and a relative value unit (RVU) weight in the Medicaid Fee Schedule calculates standardized costs in US dollars for each service adjusted for annual levels of inflation using the consumer price index.

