This study also incorporates implementation strategies from differing theoretical foundations to better understand links between the various strategies and different mechanisms which can be targeted to overcome barriers to EBP uptake, hence, ultimately leading to more precise implementation. Notably, combining REP, facilitation, and coaching to optimize CBT implementation in school settings provides an innovative way to address provider and organizational barriers, potentially maximizing EBP uptake and impact on student outcomes. In addition to determining optimal implementation strategies to embed CBT in schools for youth with depression or anxiety, this work will elucidate mechanisms of successful implementation to inform the customization of these strategies based on factors specific to different providers, organizations, and communities. Coaching and facilitation both have proven valuable and target different barriers, but the mechanisms by which they foster EBP uptake remain unknown. This study will also help elucidate if and how these implementation strategies foster frontline provider leadership, including transformational and transactional leadership skills previously studied in health care settings. Cost-effectiveness analyses will further tie differences in the cost of an implementation strategy (or adaptive sequence of strategies) to differences in important student behavioral and academic outcomes, including other forms of health care utilization and high school graduation rates.

Results from this study will also provide insight into whether improved CBT knowledge, perceptions, or skills among SPs are associated with increases in fidelity to CBT delivery and improved student outcomes. Understanding the mechanisms by which specific implementation strategies such as facilitation and coaching impact EBP uptake will inform their more precise use in different settings. The sequential randomizations embedded in the SMART design allow us to consider how different school and SP-level factors change over the course of the study and moderate the effectiveness of implementation strategies. These moderation effects can more specifically inform tailored and targeted implementation strategies improving provision of implementation support to schools as their needs change over time, and informing construction of the *most effective adaptive implementation intervention* for improving mental health outcomes across states and school districts.

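### The exploratory ICER is written with a cost difference over an undifferenced effect; both denominators should be between-intervention differences (minor, exploratory aim 1 only)

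*Protocol article*

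**What the plan says.** The Exploratory aims part of the Analyses section states that "incremental cost effectiveness ratios (ICERs) will be calculated for each relevant comparison of implementation interventions". The same sentence gives the recipe, with two denominators: "dividing the incremental average costs by the number of CBT sessions delivered as well as the number of depression or anxiety-free days". Those days are to be derived "based on PHQ-9T or GAD-7 student score changes between each time point".

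Three other places bear on it:

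- The list of exploratory aims under Aims and objectives sets the task: to "determine the incremental cost-effectiveness of added coaching and/or facilitation".
- Cost estimates, under Measures, describes the inputs: "For each implementation strategy, we will calculate the average costs and average outcomes per SP using methods described elsewhere".
- The Discussion says: "Cost-effectiveness analyses will further tie differences in the cost of an implementation strategy", and goes on to link these to differences in student behavioral and academic outcomes.

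**The concern.** An ICER answers one question: what does one more unit of effect cost when the dearer option replaces the cheaper one? Both its parts are therefore contrasts between the same two options. The article makes the cost a contrast and leaves each effect as a plain count. The result is neither an average cost-effectiveness ratio (own cost over own effect) nor an incremental one.

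Two things are at stake if an analyst follows the sentence literally. Sessions or symptom-free days that the comparator would have produced anyway could be credited to the added coaching or facilitation. And the ratio loses the ability to show that a costlier intervention is no better, or worse, because a count in the denominator does not reach zero or turn negative when the effect difference does. Cost-effective use of implementation support is one of the benefits the article claims for the adaptive approach, so the definition should be right even though the aim is exploratory.

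**Working it through.** **What the text supplies.** The article gives no ICER, no cost and no mean session count, so there is no figure to reproduce. The check is algebraic, followed by illustrations on assumed values.

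**Comparison of the statements.**

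| Place in the article | Cost term | Effect term |
|---|---|---|
| Analyses, Exploratory aims | incremental average cost | number of sessions; number of symptom-free days |
| Aims and objectives, exploratory aims | incremental cost-effectiveness of added strategies | (same) |
| Cost estimates | average per SP, each strategy | average per SP, each strategy |
| Discussion | differences in cost | differences in outcome (behavioral, academic) |

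Only the first row gives a formula, and only there is the effect term left undifferenced. The score changes mentioned in that sentence are changes over time within students. They serve to build symptom-free days and are not a contrast between interventions.

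**Algebra.** Let C1, E1 be mean cost and mean effect per SP under the costlier intervention, and C0, E0 those under its comparator.

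- ICER = (C1 − C0)/(E1 − E0)
- Ratio as written, with the costlier intervention's own count = (C1 − C0)/E1
- Quotient = E1/(E1 − E0); the cost difference cancels.

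For E1 > E0 > 0 the quotient exceeds 1, so the literal ratio understates the cost per additional unit. The two agree only when E0 = 0.

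**Are those conditions plausible here?** The Abstract says coaching and facilitation need more resources than Replicating Effective Programs (REP), so C1 > C0 is expected. REP-only schools receive the training and the CBT package, and the Sample size section assumes a 10% phase 1 response among them, so E0 > 0 is expected.

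**Illustration.** All values are assumed: C1 − C0 = $1,000 per SP, which does not affect the factor.

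| E0 | E1 | As written, 1000/E1 | ICER, 1000/(E1 − E0) | Factor |
|---|---|---|---|---|
| 0 | 20 | 50.0 | 50.0 | 1 |
| 20 | 40 | 25.0 | 50.0 | 2 |
| 20 | 30 | 33.3 | 100.0 | 3 |
| 20 | 25 | 40.0 | 200.0 | 5 |
| 20 | 21 | 47.6 | 1,000.0 | 21 |
| 20 | 20 | 50.0 | undefined | – |
| 20 | 15 | 66.7 | −200.0 (dominated) | – |

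Over assumed comparator means of 5 to 40 sessions and gains of 1 to 20, the factor runs from 25/20 = 1.25 (E0 = 5, E1 = 25) to 41/1 = 41 (E0 = 40, E1 = 41). It is largest where the gain is smallest. In the last two rows the literal ratio still looks like an ordinary cost per session.

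**Dependence on the arm chosen.** The sentence does not say whose sessions are counted. With the comparator's count as denominator, the quotient becomes E0/(E1 − E0), which is below 1 once E1 > 2·E0. For E0 = 10 and E1 = 30, that ratio is 1000/10 = 100 against an ICER of 1000/20 = 50, an overstatement. So the direction of the error also depends on a choice the text leaves open.

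**The case against.** The strongest reply is that this is loose wording in a condensed article. The sentence itself calls the measure incremental and ties it to pairwise comparisons; the aim is worded the same way; the Discussion speaks of differences on both sides, though for other outcomes than sessions. Cost estimates yields per-strategy averages, which are exactly what a standard ICER needs. The Analyses section refers to a detailed plan in Appendix 3, which is not shown. Since the literal sentence names no arm, an analyst would have to resolve it, and the name of the measure points to the standard answer.

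Most of this stands. The intent was very probably difference over difference, and the published sentence does not show that the analysis will be done wrongly. What does not stand is that nothing needs changing. An appendix can supply omitted detail, but this is a stated formula that is wrong if followed, and nothing in the article corrects it. If the appendix has it right, the two should agree.

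A reader might go further and infer that the reported ratios will be too favourable to coaching and facilitation, perhaps by a factor of three or more. The article does not support that. It would require literal use of the sentence, the costlier intervention's count as denominator, and session means that the article does not give.

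**Conclusion.** The definition is wrong as written: an incremental cost over an effect that is not incremental, at odds with the name of the measure, the stated aim and the Discussion. Used literally with the costlier intervention's own count, a positive cost difference and a comparator that delivers some sessions, it understates the cost per additional unit by the factor E1/(E1 − E0), and it cannot show dominance. The same holds for symptom-free days.

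The actual size is unknown; every number in the illustration rests on assumed means. The point is minor. It concerns exploratory aim 1 alone and leaves the primary outcome, the primary comparison, the randomizations and the sample size unaffected. That the text misstates the ratio is certain; that the analysis would follow the misstatement is not.

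**What to change.** Replace the formula in the Exploratory aims part of the Analyses section with a statement along these lines: for each pair of interventions compared, the ICER is the difference in mean cost per SP divided by the difference in mean number of CBT sessions per SP; a second ICER divides the cost difference by the difference in mean depression- or anxiety-free days. Add that where the effect difference is zero or negative, no ratio is interpreted as a cost per unit gained and dominance is reported instead. Check that Appendix 3 says the same.

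The cost is a sentence or two of text. No new data, no added sample and no change to any other analysis are needed.

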#### Missing data

Missing outcome data may occur due to school or SP dropout or loss of contact with SPs or students. Our sample retention protocol will ensure that all efforts are made to obtain primary outcome measures for all SPs in all 100 schools. For our primary SP-level outcome, based on preliminary data from TRAILS, we anticipate an attrition rate of < 10%. Prior to conducting all primary and secondary data analyses, missing data will be dealt with explicitly using multiple imputation methods for SMART studies [86, 87].

### Sample size

The estimated sample size for this study is based on our primary aim: a comparison between the expected number of CBT sessions delivered by SPs between months 1 and 18 in schools receiving the adaptive implementation intervention (REP+ coaching + facilitation for schools that are eligible) versus the control (REP only). The sample size calculation for this comparison is a straightforward adjustment to the sample size calculation for a two-sample *t* test [88]. The first adjustment accounts for the clustering of SPs within schools (estimated interclass correlation = 0.03) to account for between-site variation induced by within-site correlation in SP CBT delivery outcomes. The second adjustment accounts for the rate of response following each phase 1 treatment by weighting schools differently to account for some schools being re-randomized and contributing to multiple experimental conditions. Using a two-sided test based on *k* = 100 schools (50 randomized to REP and 50 to REP+coaching in phase 1), on average ≥ 2 SPs per school (anticipated *N* ≥ 200 SPs), a type-1 error rate of 5%, ICC = 0.03, and assuming phase I response rates of 10% (REP only) or 50% (REP+coaching), we will have > 80% power to detect a moderate effect size of *D* = 0.53 between the two implementation interventions on number of CBT sessions delivered.

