### Sites/schools

Over 200 SPs from up to 100 schools across the State of Michigan’s 900+ high schools will be recruited by study staff to participate in the study. Every attempt will be made to recruit at least one eligible school from each county in Michigan and to include rural as well as urban and suburban schools.

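### The power statement makes no allowance for the attrition of under 10% that the protocol anticipates; at 200 SPs, power drops below 80% after about 2% complete loss and to about 77% at the 10% bound

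*Protocol article*

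**What the plan says.** The Sample size section of the protocol article bases the calculation on the primary aim, the adaptive intervention against REP alone. The design is described as "Using a two-sided test based on *k* = 100 schools (50 randomized to REP and 50 to REP+coaching in phase 1"), with "on average ≥ 2 SPs per school (anticipated *N* ≥ 200 SPs"). Two adjustments to a two-sample *t* test are named. The first is for "clustering of SPs within schools (estimated interclass correlation = 0.03"). The second weights schools for re-randomization, "assuming phase I response rates of 10% (REP only) or 50% (REP+coaching"). The result is stated as more than "80% power to detect a moderate effect size of" *D* = 0.53.

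The Missing data section, just before it, deals with the same SP-level outcome. It foresees dropout of schools and SPs, says that "based on preliminary data from TRAILS, we anticipate an attrition rate of" less than 10%, and plans multiple imputation. The Sites/schools section describes recruitment as "Over 200 SPs from up to 100 schools". Nowhere does the article say that the 100 schools or 200 SPs already include an allowance for loss.

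**The concern.** The published power figure is the justification for the size of the trial. It is given with all its inputs, and the anticipated attrition stands in the adjacent section, so the two can be checked against each other. The calculation uses the numbers recruited as if all of them were analysed. If the figure had a comfortable reserve, the lack of an attrition allowance would not matter. If it sits on the 80% boundary, then over most of the attrition range that the protocol anticipates, a trial of 200 SPs would have less than the stated power for *D* = 0.53. A reader of a null result would then be relying on a planning figure slightly better than the one the design delivers.

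**Working it through.** **Inputs.** All come from the Sample size section except attrition, which comes from Missing data: two-sided α = 0.05; *k* = 100 schools, 50 per phase 1 arm; *m* = 2 SPs per school (the stated minimum), so 100 SPs per arm; ICC = 0.03; phase 1 response rates 0.10 and 0.50; *D* = 0.53; attrition below 10%.

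**Formula.** The article names the adjustments but does not print the formula. The usual form is

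- design effect = 1 + (*m* − 1) × ICC
- weighting factor per arm = 2 − response rate, i.e. 1.9 and 1.5 (sum 3.4, mean 1.7)
- SE² = 3.4 × design effect / SPs per arm
- power = Φ(*D*/SE − 1.960)

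**Reproducing the stated figure.** Design effect = 1.03. SE² = 3.4 × 1.03 / 100 = 0.03502, so SE = 0.1871. *D*/SE = 0.53/0.1871 = 2.832. Power = Φ(2.832 − 1.960) = **80.8%**. With a noncentral *t* it is 80.5% (198 df) or 80.1% (98 df). The effect detectable with 80% power is (1.960 + 0.842) × 0.1871 = 0.524. The number of schools needed for *D* = 0.53 is 4 × 2.802² / (2 × 0.53²) × 1.03 × 1.7 = 97.9.

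Weighting only the adaptive arm would give 91.0%, and no weighting 95.8%. Both exceed 80%, but 0.53 lies at the 80% boundary only when both arms are weighted. That is therefore taken as the formula used.

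**Adding attrition.** Lost SPs are assumed to contribute nothing. At 10% SP loss, *m* = 1.8, design effect = 1.024 and there are 90 SPs per arm. SE² = 3.4 × 1.024 / 90 = 0.03868, *D*/SE = 2.695, power = Φ(0.735) = 76.9%. If whole schools are lost (*k* = 90, *m* = 2), SE² = 3.4 × 1.03 / 90 = 0.03891 and power = 76.6%.

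| Loss | SP loss, normal | School loss, normal | SP loss, *t* (98 df) |
|---|---|---|---|
| 0% | 80.8% | 80.8% | 80.1% |
| 1% | 80.5% | 80.5% | 79.7% |
| 2% | 80.1% | 80.1% | 79.3% |
| 5% | 78.9% | 78.8% | 78.2% |
| 10% | 76.9% | 76.6% | 76.1% |

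By the normal approximation, power reaches 80% at 2.3% loss of SPs or 2.1% loss of schools. At 10% loss the detectable *D* is 0.551 (SPs) or 0.553 (schools).

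**What would absorb it.** With 218 SPs recruited in 100 schools, a 10% loss leaves 196.2 SPs (*m* = 1.962) and power of 80.1%. Alternatively, 109 schools of 2 SPs would be needed.

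**The case against.** The strongest reply is that the stated figure is correct for the inputs listed with it. That stands: more than 80% is reproduced, and there is no arithmetic error. Four further points also have force.

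- **Less than 10% is a bound.** The 77% is the value at a limit the protocol expects not to reach. Over 0 to 10% loss the range is about 81% to 77%.
- **The SP numbers are minimums.** The article says at least 2 per school, at least 200 in all, and over 200 at recruitment. A modest excess, to about 218, would cover a 10% loss. The article commits to no figure above 200, however, and quotes power at the minimum.
- **A lost SP is not a blank.** The outcome is a total of weekly reports, all randomized schools stay in the intent-to-treat sample, SPs are followed up by email and phone, and multiple imputation is planned. Partial data may recover some information. The documents do not allow the amount to be calculated, and imputation does not restore what was never reported.
- **The formula is inferred** from its fit to the 80% boundary, and the detailed analysis plan (Additional file 3) is not shown. A reserve of under one percentage point rests on that inference.

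A reader might infer that the power holds only if all 100 schools and all 200 SPs are analysed. The documents do not support that: by the normal approximation about 98 schools of 2 SPs suffice. A reader might also take the phrase about up to 100 schools as a ceiling in conflict with the calculation. The Abstract, Missing data and Sample size sections all treat 100 as the number, so this is at most loose wording and adds little.

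**Conclusion.** The point holds in a limited form. The power calculation has no allowance for the attrition anticipated on its own outcome, and at 200 SPs it has almost no reserve. Power at *D* = 0.53 goes from about 81% with no loss to about 79% at 5% and about 77% at the 10% bound, crossing 80% at about 2%; with a *t* reference on 98 df it crosses at or before 1%. The detectable effect moves from 0.53 to about 0.55.

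This assumes exactly 200 SPs, no information from lost SPs, and weighting of both arms. It would be wrong to infer that the trial's power is 77%: that is the figure at the bound under the least favourable treatment of missing data. The shortfall is modest and does not call the design into question, but the published figure should reflect the attrition the protocol expects.

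**What to change.** In the Sample size section, restate the figure with attrition, for example: *with 100 schools and 200 SPs, power for D = 0.53 is about 81% with no attrition and about 77% at 10% attrition, at which 80% power is available for D = 0.55.* If it is expected that partial weekly reports will recover some of this, say so there.

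Alternatively, if it is what was meant, state that 200 is the number of SPs with outcome data after attrition. At a 10% loss that implies recruiting about 200/0.9 ≈ 222 SPs, so recruitment would have to be planned to match.

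The first option costs one sentence and a slightly less favourable headline figure. It needs no extra enrolment and no change to the design or analysis.
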